## Background

Heart failure (HF) is a major clinical and public health concern. An estimated 1.3% (13.7 million) of the adult population (age  $\geq 35$  years) have HF in China. Burden of hospitalizations and health care costs among individuals with HF in China are higher than those in other low and middle income countries. About one-third of HF associated hospitalizations are triggered by respiratory infection. Considerable data support the broad benefits of influenza vaccination in the general population. However, there is uncertainty over the efficacy of influenza vaccination for preventing cardiovascular events in the high-risk patients with HF. Although Guidelines for HF management and guidelines for other cardiovascular disease management recommend influenza vaccine for patients with cardiovascular disease, there are scarce of evidence-based data as to the effect of influenza vaccination in patients with HF.

Associations between influenza and cardiovascular disease varied from study to study. In a retrospective cohort, for patients with existing congestive heart failure (CHF), the overall hospitalization rate during influenza season was 11% higher (Hazard Ratio [HR] 1.11, 95% confidence interval [CI] 1.03-1.20) than that during non-influenza season. A population-level estimate of influenza-associated excess cardiovascular hospitalization accounted for 10% (95% CI, 7%-14%) in the oldest old. However, all-cause hospitalization wasn't found to be associated with influenza vaccination in HF patients in a post hoc analysis of the Prospective Comparison of ARNI with ACEI to Determine Impact on Global Mortality and Morbidity in Heart Failure (PARADIGM-HF) study. This secondary analysis from trial data showed influenza vaccination was associated with lower risk of all-cause death (HR 0.82, 95% CI 0.70-0.96), but not with lower risk of cardiovascular death or HF-related hospitalization, or all-cause hospitalization. A nationwide cohort study suggested similar 18% reduced risk of all-cause death in HF patients receiving  $\geq 1$  influenza vaccination (HR 0.82; 95% CI, 0.81–0.84). HF inpatients with concomitant influenza infection were reported to have higher in-hospital mortality than those without concomitant influenza infection (6.2% vs. 5.4%, odds ratio [OR] 1.15, 95% CI 1.03 to 1.30). However, a data linkage study from the Get With The Guidelines – Heart Failure (GWTG-HF) quality improvement initiative showed similar 1-year all-cause mortality and 1-year all-cause readmission between influenza vaccinated HF inpatients and those unvaccinated. Given the above inconsistent results observed in different studies, definitive conclusions cannot be drawn without high quality randomized clinical trials.

Influenza vaccination is more commonly reimbursed for both the elderly and those with chronic conditions by public funding in the Americas and the Western Europe than in the Western Pacific. A government run insurance scheme for influenza vaccines seems correlates more with a higher influenza vaccine coverage rate, than with economic development status across countries. In China, the free influenza vaccine policy for people older than 60 years old is only applied in a few cities. The rate of influenza vaccination was as low as 0.6% in Chinese patients with HF, compared to about 60% in the Western European countries and in the US. Given the WHO recommendation that all people except those younger than 6 months should get influenza vaccine, the low influenza vaccine rate in China provides us a chance to study the efficacy of influenza

vaccination in reducing mortality and HF hospitalization, as neglectable low proportion of HF patients received the influenza vaccine in the routine care.

Under current vaccine regulations in China, adult immunization service can only be sought at licensed community health center or immunization clinics housed in center for disease control and prevention (CDC). Hospitals are allowed to establish a temporary Point of Vaccination (POV) after a quality check and then approval valid for three months from their local department of health. But most hospitals don't have a POV in place at the time as many of them consider vaccination being out of the scope of clinical services. Unaware of the importance of annual vaccinations, not knowing where to get vaccinated, and not wanting to pay are the top barriers prohibiting those with chronic conditions from getting influenza vaccines. Thus, it is of critical importance to investigate whether improved influenza vaccine coverage rate in patients with HF will reduced all-cause death or HF hospitalization. Before investigating the efficacy of influenza vaccines on preventing cardiovascular disease, we need to first address whether educating patients and health provider, providing vaccination service in hospital, and providing free influenza vaccine will achieve a target vaccine coverage rate (VCR) among patients hospitalized due to severe symptoms of HF.

Before a definitive cluster randomized trial, a pilot feasibility study is planned to address the following uncertainties: 1) Whether the intervention package is feasible; 2) Whether a target influenza vaccine rate of 90% is achievable in the intervention clusters; 3) Proportion of patients hospitalized with HF getting influenza vaccination in routine care; 4) Number of patients will be enrolled in future study.

## **Methods**

This protocol follows the extension to CONSORT 2010 statement on reporting pilot and feasibility trials, the SPIRIT 2013 statement on standard protocol items for clinical trials, and its explanation and elaboration report.

### **Trial design**

This pilot trial is a two-arm, parallel, hospital-based, cluster randomized trial where 7 hospitals will be randomized to intervention and 4 hospitals to control arm. All eligible HF inpatients from each hospital will be recruited during 2020 November. Intervention includes (i) education of the health care team and patients; (ii) provision of free vaccine on the day of discharge; and (iii) provision of immunization service inside hospital before discharge.

### **Setting**

PANDA II pilot will be conducted in county-level hospitals in Henan Province, China. County-level hospitals serve a relatively fixed population living in the corresponding geographic area, which to the largest extent prevents recruiting the same patients seeking care in different participating centers.

#### Inclusion criteria for participating sites:

- 1) capable of admitting and treating HF patients;

- 2) with the capacity of treating >35 HF patients per month during recruitment period;
- 3) staff with available care team personnel to collaborate.
- 4) local approval to provide influenza vaccination from administrative bureau/ center for disease control and prevention (CDC).

Exclusion criteria for participating sites:

Participation in a vaccination-related HF patient outcome improvement programs that might confound study outcomes.

**Patients**

PANDA II pilot trial will focus on HF patients at higher risk of having serious complications from influenza infection. HF is largely a clinical diagnosis. Based on the widely used Boston criteria, HF will be defined according to the attending physician's report of any of the following clinical symptoms described as dyspnea ('unusual' on light exertion or recurrent in the supine position); fluid retention; description of 'rales' in the lungs, jugular venous distension, or pulmonary edema on physical examination; or pulmonary edema on chest x-ray presumed related to cardiac dysfunction. HF patients will be identified through screening the admission list of a cardiovascular ward in each participating hospital for the following eligibility criteria.

Inclusion criteria for participating patients:

- 1) all the adult inpatients (age  $\geq 18$  years) with a discharge diagnosis of HF during recruitment month in participating hospitals;
- 2) assessed as New York Heart Association (NYHA) function classification III-IV during hospitalization;
- 3) consent to participate in the study.

Exclusion criteria for participating patients:

- 1) have known allergy to influenza vaccine.
- 2) pregnant women.

**Intervention**

The intervention will include three components:

- 1) education to all members of the health care team, physicians, nurses, and patients;
  - a. A 30-minute training session to health care teams in all participating hospitals after they are included in the study. Members in a health care team include site investigators, physicians, and nurses. The training session include the association between influenza vaccine and lower risk of mortality and rehospitalization in patients with HF, the study protocol, and current regulations on vaccine circulates. The education material will be designed and delivered by study investigators.
  - b. Study nurses in each participating hospital will lead a 15-minute group or individual training session to patients after they reach a relative-stable status during hospitalization. The training sessions include plain language version content on association between influenza infection and

cardiovascular disease and current guideline recommendations of influenza vaccine for secondary prevention in patients with established cardiovascular disease. The training material (presentation slides, scripts, and videos) will be designed and delivered by study investigator.

- 2) provision of free influenza vaccine on the day of discharge;
- 3) provision of immunization service inside hospital before discharge and a minimum of 1 hour after vaccination and before discharge to observe any potential adverse events of the vaccination.

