| Rationale              | 
Considerable data support the broad benefits of influenza vaccination in the general population. However, there is uncertainty over the effectiveness of influenza vaccination in preventing cardiovascular events in the high-risk population such as those with HF. Influenza vaccination is not covered by medical insurance in majority of China. The rate of influenza vaccination was as low as 0.6% in Chinese patients with HF, compared to about 60% in the Western European countries and in the US. Thus, it is of critical importance to detect whether providing free influenza vaccine, providing vaccination service in hospital, and educating patients as well as health provider will increase vaccine rate among patients hospitalized due to severe symptoms of HF. If so, whether improved influenza vaccine rates in patients with HF will reduced all-cause death or HF hospitalization. Before a definitive randomized cluster randomized trial, a pilot study is planned to address the following uncertainties for the design of future definitive study:
 
 
(i) Whether the intervention package is feasible;
 
(ii) Whether a target influenza vaccine rate of 90% is achievable in the intervention clusters;
 
(iii) Proportion of patients hospitalized with HF getting influenza vaccination in routine care;
 
(iv) Number of patients will be enrolled in future study.
 
 |

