### **Comparator**

Currently the routine practice is that HF patients discharged from hospitals seek and pay for influenza vaccination service in community health center or immunization clinic at local CDC.

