### **Sample size**

As this is a pilot trial and the primary objective is to test the feasibility of increasing influenza vaccination uptake in HF patients, other than to test the efficacy or effectiveness of intervention, a practical number of 11 participating sites and inpatients

with HF during one month (30 patients on average) from each site are set. Intra-cluster correlation coefficient of 3-month death or rehospitalization due to heart failure will be calculated using the outcome of each individual from each cluster.

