| TIMEPOINT                                                                 | November                                  | December   | January         | February | March | April     |
| ENROLMENT:                                                         |                                           |            |                 |          |       |           |
| Hospital and patients eligibility screen                                  | X                                         |            |                 |          |       |           |
| Hospital and patients informed consent                                    | X                                         |            |                 |          |       |           |
| Allocation                                                                |                                           | X          |                 |          |       |           |
| INTERVENTIONS:                                                     |                                           |            |                 |          |       |           |
| [Intervention arm (education + vaccination)]                       |                                           | X          |                 |          |       |           |
| [Control arm (usual care)]                                         |                                           | X          |                 |          |       |           |
| ASSESSMENTS:                                                       |                                           |            |                 |          |       |           |
| [baseline demographics, clinical characteristics, and vaccination] | X                                         | X          |                 |          |       |           |
| [recruitment rate]                                                 | X                                         | X          |                 |          |       |           |
| [vaccination logistics, immunization service license]              |                                           |            | X               | X        |       |           |
| [adherence rate]                                                   |                                           |            |                 | X        | X     |           |

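### The education component is worded for all 11 randomised hospitals, while the design and Figure 1 assign it to the intervention arm and call control usual care; followed literally, control uptake would not estimate routine care.

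*Protocol*

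**What the plan says.** **Who is educated.** Protocol, Intervention, item 1a: "A 30-minute training session to health care teams in all participating hospitals after they are included in the study". On content: "The training session include the association between influenza vaccine and lower risk of mortality and rehospitalization in patients with HF, the study protocol", together with the rules on vaccine circulation. Item 1b: "Study nurses in each participating hospital will lead a 15-minute group or individual training session to patients", covering the link between influenza and cardiovascular disease and the guideline recommendations for vaccination.

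**What education is.** Trial design: "Intervention includes (i) education of the health care team and patients". The Synopsis (Intervention row) lists the same three components. Figure 1 labels the intervention arm as education plus vaccination.

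**What control is.** Comparator: "Currently the routine practice is that HF patients discharged from hospitals seek and pay for influenza vaccination service" at a community health center or local CDC clinic. Figure 1 labels the other row "Control arm (usual care". Neither mentions education.

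**What the control arm is needed for.** One of the four pilot questions in the Synopsis and Background is: "Proportion of patients hospitalized with HF getting influenza vaccination in routine care". Outcomes lists vaccine uptake in the intervention hospitals and in the control hospitals as a primary outcome.

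**The concern.** Education is one of the three components being randomised. If 1a and 1b are carried out as worded, the 4 control hospitals receive that component, and only the free vaccine and the in-hospital service separate the arms. Control uptake would then describe patients whose doctors, nurses and they themselves had been taught the case for vaccination, and who still had to find and pay for it elsewhere.

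The Background names lack of awareness of the importance of annual vaccination among the top barriers, and education acts on that directly. The site exclusion criteria keep out hospitals in vaccination-related programmes because these might confound the outcomes; the literal wording would bring a similar exposure into the trial's own controls.

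Sites could also read the text differently from one another. With only 4 control hospitals, that could leave a mixed comparator that nobody could describe afterwards. Once control staff have been trained, it cannot be undone.

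**Working it through.** **1. Does participating mean all sites or one arm?**
- Sample size: "a practical number of 11 participating sites and inpatients", so all 11.
- Randomization: participating sites are the units randomised, so both arms.
- Patients: admission lists are screened in each participating hospital, so both arms.
- Where the protocol means one arm, it says intervention hospitals (Outcomes, Participant timeline, Randomization).

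On the protocol's own usage, 1a and 1b cover both arms.

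**2. When is the staff session given?** Item 1a ties it to inclusion in the study, not to allocation. Figure 1 puts hospital screening and consent in November and allocation in December. A session triggered by inclusion could therefore precede allocation and could not be arm-specific.

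**3. Is 1a only procedural training?** No. It covers the study protocol but also the association of vaccination with lower mortality and rehospitalisation. Data monitoring separately provides study-procedure training for research staff at any participating center before initiation, so control hospitals do not need 1a for that purpose.

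**4. The passages side by side.**

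| Place | Education in control hospitals? |
|---|---|
| Intervention, 1a and 1b | Yes, read literally |
| Synopsis and Trial design | No; education is part of the intervention |
| Comparator | No; routine practice |
| Figure 1 | No; education is in the intervention row, control is usual care |

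**5. Size.** Inputs from the protocol: 11 hospitals, average 30 patients, 7 intervention and 4 control hospitals, cited uptake 0.6%, target 90%.
- Stated total: 11 × 30 = 330, which reproduces. Control arm: 4 × 30 = 120.
- Expected vaccinated controls at 0.6%: 120 × 0.006 = 0.72. Chance of none, ignoring clustering: (1 − 0.006)^120 = 0.49.
- One additional vaccinated control patient moves the estimate by 1/120 = 0.83 percentage points, more than the whole cited rate.
- The protocol gives no effect of education alone. The uptakes below are assumptions, chosen to show a range. Intervals are exact binomial and ignore clustering.

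| Assumed control uptake | Vaccinated of 120 | 95% interval | Multiple of 0.6% | Contrast with 90% |
|---|---|---|---|---|
| 5% | 6 | 1.9% to 10.6% | 5/0.6 = 8.3 | 85 points |
| 10% | 12 | 5.3% to 16.8% | 10/0.6 = 16.7 | 80 points |
| 20% | 24 | 13.3% to 28.3% | 20/0.6 = 33.3 | 70 points |

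At 0.6% the contrast is 90 − 0.6 = 89.4 points. Relative to its own size the routine-care estimate could shift many-fold, while the contrast between arms stays large.

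**The case against.** **The wording may only be loose.** Items 1a and 1b stand under a heading that describes the intervention. Components 2 and 3 in the same list carry no arm restriction either, and nobody would read them as free vaccine for controls, because the Participant timeline and Randomization tie vaccination to intervention hospitals. Item 1b can be read in the same way. Figure 1 expressly places education in the intervention arm, and every site has to be taught the study protocol. This stands to the extent that the intended design is probably education in the intervention arm only. It does not cure 1a, which says all participating hospitals, is timed from inclusion, and is the text that staff would follow.

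**The pilot does not test effectiveness.** Sample size says so, and the analysis is descriptive. The 90% target concerns intervention clusters only, and the other pilot questions do not depend on control uptake. This stands, and it confines the harm to pilot question (iii), the control half of the primary outcome, and what the contrast means.

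**Stronger readings that a reader might infer.**
- That control hospitals will be educated. The documents do not settle this; they contradict each other.
- That the trial cannot measure routine-care uptake at all. Too absolute: even on the literal reading, control patients would still seek and pay for vaccination, so the result is an estimate with a probable upward bias of unknown size.
- That the definitive trial would be mis-sized by a calculable amount. Scaling sample size by 1/contrast² gives (89.4/85)² = 1.11, (89.4/80)² = 1.25 and (89.4/70)² = 1.63. But this needs the assumed education effects and a clinical effect that is linear in the uptake contrast, neither of which is in the protocol. An overstated control rate would also make a trial with true usual-care controls too large, not underpowered.

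**Conclusion.** The point holds as an internal contradiction in operative text. The Intervention section writes staff and patient education for all 11 randomised hospitals; the Synopsis, Trial design, Comparator and Figure 1 describe a control arm without it. Carried out literally, control uptake would estimate education plus self-paid vaccination, and would probably be too high as an estimate of routine care.

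The direction rests on the premise that education does not lower uptake. The size cannot be derived from the protocol, and the 8- to 33-fold range is illustrative only. What does follow from the protocol's own figures is how fragile the estimate is: with 0.72 expected vaccinations among 120 controls, a handful of prompted ones would determine it. The ambiguity should be removed before any control site is trained.

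**What to change.** Reconcile Trial design, Intervention, Comparator and Figure 1:
- Reword 1a and 1b so that the vaccine-benefit staff training and the patient session are given only in the 7 intervention hospitals, after allocation.
- State that the 4 control hospitals receive study-procedure training only, as Data monitoring already provides.
- If education in both arms is what the sponsor intends, relabel the control arm as education only in the Comparator and Figure 1, redefine the intervention as the free vaccine and the in-hospital service, and drop the claim to estimate uptake in routine care.

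The first option costs about two sentences in the protocol and a split slide set, with no extra patients or staff. The second costs only text, but gives up pilot question (iii).

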### **Comparator**

Currently the routine practice is that HF patients discharged from hospitals seek and pay for influenza vaccination service in community health center or immunization clinic at local CDC.

### **Outcomes**

#### *Primary outcome*

- Rate of uptake of influenza vaccination among eligible patients in the intervention hospitals and that in the control hospitals;
- Number of patient recruited;
- Rate of adherence to follow-up;

#### *Secondary outcome*

- Influenza-like illness (ILI) rate; influenza-like illness is defined as an acute respiratory illness with a measured temperature of  $\geq 38^{\circ}\text{C}$  and cough, within the past 10 days. 
- Death or readmission for heart failure rate over 3 months follow-up through face-to-face or phone call follow-up.

